### Sample size

From a previous trial on assessing the efficacy of group-based behavioural activation with mindfulness for treating subthreshold depression in primary care in Hong Kong, mean (standard deviation) of BDI-II score at baseline for intervention and usual group were 19.18 (8.35) and 17.68 (9.52) respectively among participants with subthreshold depression. Pooled mean and standard deviation were 18.43 and 8.95 from two groups. For moderate baseline severity, the minimum clinically important difference (MCID) on the BDI-II was estimated at 3.5 points [24]. Assuming at least the MCID could be seen in the online exercise programme at 4-month post randomisation compared to usual care, sample size of 104 each group achieve 80% power to detect the difference of 3.5 points in BDI-II with a common standard deviation of 8.95 at a significance level of 0.05 using two-sided t-test. The corresponding effect size of 0.39 is similar to the finding from a systematic review that physical activity is beneficial for improving depressive symptoms with effect size of 0.43 [8]. From our experience in running online exercise intervention for people with subthreshold depression, a dropout rate of 13% at 12 month follow up was observed. To be conservative, we assume drop out to be 20%, and set our enrolment target at participants in total of 260 with 130 participants in each group.

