### Intervention: Online exercise programme

The design of the exercise class (duration and frequency) is modified from the class for diabetes and hypertension based on findings from recent systematic reviews on the effectiveness of physical activity intervention for improving depression and anxiety [8]. The 12-week EIM program aims to transform participants' exercise habits by fostering and maintaining behavioural changes through motivation, as well as providing relevant knowledge and experience. The online classes will be conducted by certified physical trainers who hold a post-secondary degree (or equivalent), possess a valid basic life support certificate, and have been certified by the Physical Fitness Association of Hong Kong after passing examinations. They have also completed specialized training to deliver the EIM program.

The 12-week EIM online class on the Zoom platform (details in Appendix 1) will enrol 11 to 18 patients per group and meet twice a week for 1 h each time. Each class contains a set of exercises including stretching, aerobic exercise and resistance training (combined exercise) and will be carried out according to specific protocol [17] (Appendix 1). Participants will receive reminders about each session via WhatsApp or telephone calls. After each class, home exercises were assigned to achieve a minimum of 150 min of exercise per week. Additionally, regular SMS or WhatsApp messages will be sent to remind and encourage participants to incorporate exercise into their daily routines. Furthermore, participants will also be provided with smartwatches to track their physical activities. The trainers can monitor participants' activity levels via trackers before each lesson, enabling them to motivate individuals and address barriers as needed, thereby offering regular reinforcement, social support, and problem-solving assistance. Zoom lessons will be recorded, and approximately 15% of these recordings will be reviewed by the investigator to ensure fidelity to the intervention.

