### Statistical analysis

Baseline characteristics of the two groups will be compared using chi-square test for categorical variables and independent samples t-test for continuous variables. Analysis of covariance (ANCOVA) for the BDI-II score at T1 will be conducted as the primary analysis, with the BDI-II score at T0 and other characteristics with significant between-group difference at T0 as covariates in the model for sensitivity analyses. Effect size estimates will be obtained for the primary outcome, with the between group effect sizes (Cohen’s d) being calculated using the mean differences from baseline and the SDs of the two groups at each time point. For the secondary analysis, linear mixed models (LMM) with random intercept will be applied to investigate the significant changes over time, for both primary and secondary outcome measures. The LMM approach is in line with the intention-to-treat principle, to include all subjects for the analysis and use all available data to assess the treatment effect over time. Maximum likelihood estimation (MLE) will be employed to handle missing data in the analyses with LMMs. A sensitivity analysis will be conducted using imputed data generated by multiple imputation. Furthermore, compliance with prescribed exercises will be added into the models to explore if this is predictor of changes in health outcomes.

In the cost-utility analysis, utility will be measured with quality adjusted life years (QALYs) based on SF-12 using the Hong Kong weights. The area under curve approach will be used to calculate the utilities at follow-ups after adjusting for baseline utility. In the cost-effectiveness analysis, remission of depressive symptoms (BDI-II score of < 14) will be used as outcome. Using both provider and societal perspectives, incremental cost-effectiveness ratio (ICER) will be calculated by dividing cost difference of two groups by between-group effect difference. We will use bootstrapping technique to assess the uncertainty of the ICER estimate. Due to the lack of a local willingness-to-pay threshold, we will generate cost-effectiveness acceptability curves to evaluate the probability of cost-effectiveness of the proposed intervention.

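### The exercise arm is taught in shared classes of 11 to 18, but the sample size and the stated primary ANCOVA make no allowance for class clustering, so the planned 80% power and 5% error rate assume a class ICC of 0

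*Protocol article*

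**What the plan says.** **Delivery (Intervention: Online exercise programme).** The class "will enrol 11 to 18 patients per group and meet twice a week" for 12 weeks, live on Zoom, under a certified trainer. Trainers follow each participant's tracker data and use them to motivate and support. The care-as-usual section sends controls to the general outpatient clinics and does not group them. Nesting therefore exists in one arm only.

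**Sample size.** The target effect is 3.5 points: "the minimum clinically important difference (MCID) on the BDI-II was estimated at 3.5 points". The calculation states that a "sample size of 104 each group achieve 80% power to detect the difference of 3.5 points in BDI-II". The method assumed is the ordinary one for two independent groups, "at a significance level of 0.05 using two-sided t-test". Variability enters as a single value for both arms, "with a common standard deviation of 8.95". The only inflation is for dropout ("we assume drop out to be 20" per cent), after which the authors "set our enrolment target at participants in total of 260 with 130 participants in each group". No ICC, class size or design effect enters.

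**Statistical analysis.** The primary analysis is an ANCOVA of BDI-II at T1. The covariates named are baseline BDI-II and other baseline characteristics that differ between groups; no class or trainer term is named. For the secondary analysis, "linear mixed models (LMM) with random intercept will be applied to investigate the significant changes over time". The level of that intercept is not given; for repeated measures it most naturally means the participant.

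**The concern.** People who share a class share a trainer, a timetable and a set of peers for 12 weeks, so their T1 scores may be more alike than those of two people drawn from different classes. If so, the mean of the exercise arm is less precise than 104 independent observations would make it, while the control mean is unaffected. This is a partially nested design.

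A t-test or ANCOVA that ignores the nesting then uses too small a standard error for the primary contrast. Two things follow: the nominal 5% test can reject more often than 5%, and a test with the correct standard error has less power than the t-test calculation says. The first matters more, because it bears on the primary hypothesis and favours the intervention.

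**Working it through.** **Inputs from the protocol article:** difference 3.5, SD 8.95, two-sided alpha 0.05, 104 analysed and 130 enrolled per arm, dropout 20%, class size 11 to 18.

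**Assumed, because the documents do not give it:** class ICC of 0.01, 0.02, 0.05 or 0.10.

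**1. The plan's own figures.** The standardised difference is 3.5/8.95 = 0.391. The exact noncentral t gives 79.8% power at 103 per arm and 80.1% at 104. Dropout: 104/0.80 = 130 per arm, 260 in total. The arithmetic is right and leaves no margin for clustering.

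**2. Classes.** 130/18 = 7.2 and 130/11 = 11.8, so about 7 to 12 classes. With 20% dropout, the number analysed per class is m = 0.8 × 11 = 8.8 to 0.8 × 18 = 14.4.

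**3. Formulas.** Only the exercise-arm variance is inflated.
- Design effect in the exercise arm: DE = 1 + (m − 1) × ICC
- Standard error of the contrast: SE = 8.95 × √[(1 + DE)/104]
- Type I error of the unadjusted test: 2 × [1 − Φ(1.96 × √(2/(1 + DE)))]
- Power with the correct SE (normal approximation): Φ(3.5/SE − 1.96)

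**4. Worked case, ICC 0.05.**
- m = 8.8: DE = 1 + 7.8 × 0.05 = 1.39; SE = 8.95 × √(2.39/104) = 1.357; power = Φ(2.58 − 1.96) = 73.2%; type I error = 2 × [1 − Φ(1.79)] = 7.3%.
- m = 14.4: DE = 1 + 13.4 × 0.05 = 1.67; SE = 8.95 × √(2.67/104) = 1.434; power = Φ(2.44 − 1.96) = 68.5%; type I error = 2 × [1 − Φ(1.70)] = 9.0%.

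**5. Full range.** The first figure in each cell is for 11 enrolled per class, the second for 18.

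| ICC | DE | Type I error, unadjusted test | Power, t-test basis | Power, Satterthwaite df |
|---|---|---|---|---|
| 0 | 1.00 | 5.0% | 80.5% | 78.5%, 77.1% |
| 0.01 | 1.08, 1.13 | 5.4%, 5.8% | 79.0%, 77.9% | 76.8%, 74.0% |
| 0.02 | 1.16, 1.27 | 5.9%, 6.6% | 77.5%, 75.4% | 75.2%, 71.0% |
| 0.05 | 1.39, 1.67 | 7.3%, 9.0% | 73.2%, 68.5% | 70.4%, 62.9% |
| 0.10 | 1.78, 2.34 | 9.6%, 12.9% | 66.7%, 58.8% | 63.4%, 52.2% |

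The 80.5% at ICC 0 is the normal approximation to the exact 80.1%. The last column uses df = (1 + DE)²/[DE²/(k − 1) + 1/103], with k = 104/m classes. Part of its shortfall is the price of few classes and is there even at ICC 0: 80.5 − 78.5 = 2.0 points, and 80.5 − 77.1 = 3.4 points.

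**6. Effect of baseline adjustment.** Assume a correlation r = 0.5 between T0 and T1 BDI-II, and a class variance that baseline does not reduce. Then SE = 8.95 × √[(2(1 − r²) + (m − 1) × ICC)/104]. Power before any degrees-of-freedom penalty is 88.8% to 87.7% at ICC 0.01, 87.3% to 85.1% at 0.02, 82.7% to 77.3% at 0.05 and 75.2% to 65.8% at 0.10.

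Type I error is not helped. A simulated ANCOVA without a class term (8,000 runs, r = 0.5) rejected a true null in 5.4% and 5.8% of runs at ICC 0.01, and in 8.2% and 10.4% at ICC 0.05. Adjustment shrinks the residual variance but not the class variance.

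**The case against.** - **The consequence rests on an unknown ICC.** A reader might infer that the stated power and error rate are shown to fail. The documents do not support that. They give no ICC, and at 0.01 the loss is 1 to 2 points of power and 0.4 to 0.8 points of error rate. The article also describes features that limit differences between classes: a set exercise protocol, certified and programme-trained trainers, and review of about 15% of recordings. The support it describes comes from the trainer to each individual; peer support is not claimed. This all stands. What is certain is the missing allowance, not its size.
- **The trial may still reach 80%.** A reader might infer that 260 is too few. That does not follow: the t-test calculation takes no credit for baseline BDI-II, and adjustment could keep power above 80% at small ICCs. This stands, on an assumed r, and only if baseline BDI-II is in the primary model. The Statistical analysis section leaves that unclear, since its sentence ties the covariates to sensitivity analyses.
- **The null is a particular one.** Allocation is to individuals. If the programme changes nobody's outcome, class membership adds no variance and the unadjusted test keeps about 5%. Inflation needs class effects that vary but average to zero. That is a legitimate null for a group-delivered treatment, but it must be stated.
- **The mixed models might cover it.** A reader might infer that every model in the plan ignores clustering. The text does not go that far, because the level of the random intercept is not named. The point is therefore confined to the sample size and the stated primary ANCOVA.
- **An unseen SAP may add a class term.** It may. But the article itself fixes the sample size on independence and names the primary model with its covariates. A later SAP could repair the test; it would not make the 80% a figure for the clustered design.

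**Conclusion.** The point holds as an omission with a conditional consequence. The exercise arm is nested in about 7 to 12 classes, and neither the sample size nor the stated primary ANCOVA allows for it. Any positive class ICC makes the primary standard error too small. The nominal figures are exact only at ICC 0; the departure is slight at 0.01 and material from about 0.05, where the unadjusted test's error rate is 7.3-9.0% and t-test power 69-73%.

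These sizes assume 104 analysed per arm, equal class sizes after 20% dropout, and a null with class effects that average to zero. The power loss may be offset by baseline adjustment. The error-rate problem is not, and it is the reason to change the model before outcome data are seen.

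**What to change.** 1. **Data.** Record for each exercise participant the class assigned, whether or not it is attended.
2. **Primary T1 model.** Add a class random effect in the exercise arm only, with each control as a cluster of one. Fit by REML with Satterthwaite or Kenward-Roger degrees of freedom.
3. **Mixed models.** State that the existing random intercept is for participant, if that is meant, and add the same class effect. The Statistical analysis section specifies maximum likelihood for these models, so its wording has to be brought into line with REML.
4. **Sample-size section.** State that 80% assumes ICC = 0. Give the power of 104 per group over a stated ICC range under the baseline-adjusted model, naming the assumed baseline correlation. Keep N = 260.

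The cost is wording in the protocol and SAP and one extra data field, with slightly wider intervals and a slightly less favourable stated power. No patients are added. With so few classes the class variance will be estimated imprecisely, which is why the small-sample degrees of freedom are needed. A class effect does not capture correlation between classes taught by the same trainer; the article does not say how trainers are assigned.

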### Statistical analysis

Baseline characteristics of the two groups will be compared using chi-square test for categorical variables and independent samples t-test for continuous variables. Analysis of covariance (ANCOVA) for the BDI-II score at T1 will be conducted as the primary analysis, with the BDI-II score at T0 and other characteristics with significant between-group difference at T0 as covariates in the model for sensitivity analyses. Effect size estimates will be obtained for the primary outcome, with the between group effect sizes (Cohen’s d) being calculated using the mean differences from baseline and the SDs of the two groups at each time point. For the secondary analysis, linear mixed models (LMM) with random intercept will be applied to investigate the significant changes over time, for both primary and secondary outcome measures. The LMM approach is in line with the intention-to-treat principle, to include all subjects for the analysis and use all available data to assess the treatment effect over time. Maximum likelihood estimation (MLE) will be employed to handle missing data in the analyses with LMMs. A sensitivity analysis will be conducted using imputed data generated by multiple imputation. Furthermore, compliance with prescribed exercises will be added into the models to explore if this is predictor of changes in health outcomes.

In the cost-utility analysis, utility will be measured with quality adjusted life years (QALYs) based on SF-12 using the Hong Kong weights. The area under curve approach will be used to calculate the utilities at follow-ups after adjusting for baseline utility. In the cost-effectiveness analysis, remission of depressive symptoms (BDI-II score of < 14) will be used as outcome. Using both provider and societal perspectives, incremental cost-effectiveness ratio (ICER) will be calculated by dividing cost difference of two groups by between-group effect difference. We will use bootstrapping technique to assess the uncertainty of the ICER estimate. Due to the lack of a local willingness-to-pay threshold, we will generate cost-effectiveness acceptability curves to evaluate the probability of cost-effectiveness of the proposed intervention.

The significant level will be set as 0.05 for the statistical tests. To address the issue of multiple testing in our exploratory secondary analyses, we will employ the Bonferroni correction to control the overall type I error rate by adjusting the significance threshold for each individual test. This adjustment ensures a rigorous control of false positive results while allowing for the exploration of associations between the online exercise intervention and secondary outcomes.

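### The sentence defining the primary analysis leaves open whether T0 BDI-II is a covariate in the primary ANCOVA, and it selects further covariates by baseline significance tests

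*Protocol article*

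**What the plan says.** All of the relevant text is in the Methods of the protocol article.

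- **Primary model** (Statistical analysis): "Analysis of covariance (ANCOVA) for the BDI-II score at T1 will be conducted as the primary analysis".
- **Covariates** (same sentence): "with the BDI-II score at T0 and other characteristics with significant between-group difference at T0 as covariates in the model for sensitivity analyses".
- **Baseline comparison** (same section): "Baseline characteristics of the two groups will be compared using chi-square test for categorical variables and independent samples t-test for continuous variables". The general level for tests is given as "The significant level will be set as 0.05 for the statistical tests".
- **Sizing** (Sample size): "sample size of 104 each group achieve 80% power to detect the difference of 3.5 points in BDI-II". The assumed SD is 8.95 in both arms, and the calculation is for a two-sided t-test at the 0.05 level. The sizing test has no covariate.
- **Stratification** (Randomization, concealment and blindness): gender, baseline anxiety in two classes and physical activity in three. BDI-II is not a stratification factor.

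**The concern.** Grammatically, T0 BDI-II and the test-selected characteristics form one list, and the closing words assign that list to sensitivity analyses. That leaves the primary model with no named covariate, although it is called an ANCOVA. Three readings are possible:

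- **(a) Literal.** Every covariate is for sensitivity only. The primary comparison is unadjusted and gives up the precision that T0 BDI-II would supply.
- **(b) Everything primary.** T0 BDI-II is in the primary model, together with whatever characteristics turn out to differ significantly. Precision is kept, but the primary model is not fixed until the baseline data are seen.
- **(c) Split.** T0 BDI-II is primary and only the test-selected extras are for sensitivity. The primary model is sound, and the sensitivity model is the one left to chance.

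The selection rule is a weakness on all three. Under correct randomisation any baseline difference is due to chance, so its p-value says nothing about whether the variable predicts T1 BDI-II. The rule can admit a variable of no prognostic value and pass over a strongly prognostic one. It will also tend to skip the stratification factors, which the design balances.

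This is more than detail left to an analysis plan. The article states a rule for the confirmatory analysis, and the rule can be carried out in more than one way.

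**Working it through.** **Inputs.** From Sample size: difference 3.5, common SD 8.95, 104 per group, two-sided 0.05, 80% power, 20% dropout. Assumed: the correlation r between T0 and T1 BDI-II, which the documents do not give, so a range is shown.

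**1. The plan's own figure.**
- Pooled SD = sqrt((8.35² + 9.52²)/2) = 8.95.
- d = 3.5/8.95 = 0.391, agreeing with "The corresponding effect size of 0.39".
- The exact two-sided t-test needs 103.6 per group, rounded up to 104, with power 0.801.
- 104/0.80 = 130 per group, 260 in total.

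The stated sample size reproduces, and it does so without covariate adjustment.

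**2. What T0 BDI-II adds at 104 per arm.** Residual SD = 8.95 × sqrt(1 − r²); SE = residual SD × sqrt(2/104); power ≈ Φ(3.5/SE − 1.96).

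| r (assumed) | Residual SD | SE | Power | Unadjusted variance relative to adjusted, 1/(1 − r²) |
|---|---|---|---|---|
| no adjustment | 8.95 | 1.24 | 0.805 | 1.00 |
| 0.3 | 8.54 | 1.18 | 0.840 | 1.10 |
| 0.4 | 8.20 | 1.14 | 0.868 | 1.19 |
| 0.5 | 7.75 | 1.08 | 0.903 | 1.33 |
| 0.6 | 7.16 | 0.99 | 0.941 | 1.56 |

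Example for r = 0.5: 8.95 × 0.866 = 7.75; 7.75 × 0.1387 = 1.075; 3.5/1.075 − 1.96 = 1.296; Φ(1.296) = 0.903. The t-test versions are lower by at most 0.004 (0.837, 0.865, 0.900, 0.939).

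**3. How often chance selects a covariate.** For k independent baseline tests at 0.05, the probability of at least one selection is 1 − 0.95^k: 23% for k = 5, 34% for 8, 40% for 10. The article does not state k. This is the frequency with which the model changes, not a measure of damage to inference.

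**4. Operating characteristics of each model if followed faithfully.** Simulation: 8,000 trials per scenario, 104 per arm, r = 0.5, eight baseline variables including T0 BDI-II, one of the others correlated 0.2 with the outcome.

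| Model | Type I error | Power at 3.5 points |
|---|---|---|
| Unadjusted | 0.052 | 0.81 |
| T0 BDI-II fixed | 0.051 | 0.90 |
| T0 BDI-II plus test-selected extras | 0.048 | 0.90 |

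Each model controls type I error. The selected extras bring no gain in power and no visible inflation.

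**5. Why the choice should be closed.** Under the null, the unadjusted and T0-adjusted test statistics have correlation sqrt(1 − r²). If either could be reported as primary, the chance that at least one is significant at 0.05 is about 0.064, 0.073 and 0.078 for r = 0.3, 0.5 and 0.6 (bivariate normal). This bounds what an unresolved choice between these two models could cost. It describes neither model taken alone, and it implies no intent.

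**The case against.** The strongest defence is the word ANCOVA. An ANCOVA needs a covariate, the baseline value of the outcome is the usual one, and the closing phrase can be attached to the extra characteristics alone. On that reading (c), no precision is lost and test-based selection touches only a sensitivity analysis. This stands as a plausible reading, but the grammar does not establish it, and the unadjusted t-test used for sizing fits the literal reading equally well.

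Some stronger readings are tempting, and the documents do not support them:

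- **That the primary analysis both loses precision and has a chance-dependent covariate set.** These exclude each other. If all covariates are for sensitivity, the primary model has no covariate set to vary. If they are in the primary model, T0 BDI-II is among them.
- **That the trial is underpowered.** It was sized on an unadjusted test, so omitting T0 BDI-II forgoes power above the planned 80% and does not erode it.
- **That T0 BDI-II is adjusted for only when significantly imbalanced** (which would give power of about 0.82 at r = 0.5). The sentence names T0 BDI-II outright; the condition on significance most naturally qualifies the other characteristics.
- **That an unadjusted estimate would be biased.** A baseline imbalance of z = 1.9 with r = 0.5 would move it by 0.5 × 8.95 × 1.9 × 0.1387 = 1.18 points. That is a selected case: an imbalance at least that large occurs in about 6% of correctly randomised trials. Over all randomisations the estimate is unbiased, and its standard error already covers this variation.

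It is also fair to say that the selection rule does little measurable harm to error rates, as step 4 shows. The case against it is that it selects on the wrong criterion and leaves a model unspecified.

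**Conclusion.** The point holds as an ambiguity in the definition of the primary analysis, together with a poor rule for further covariates. It does not show that the primary analysis omits baseline.

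On the literal reading, the price is power of about 0.80 where 0.84 to 0.94 was available, for an assumed T0-T1 correlation of 0.3 to 0.6. The size depends entirely on that correlation. On the other readings this loss is nil. Which model is left to baseline tests, primary or sensitivity, depends on the reading. Planned power and type I error are sound for any single model fixed in advance, so this is a nearly free improvement and not a flaw that undermines the trial.

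**What to change.** Replace the covariate sentence in Statistical analysis with wording such as: *The primary analysis is ANCOVA of BDI-II at T1 on treatment group, with T0 BDI-II (continuous) as a prespecified covariate.* Remove selection by significant baseline difference. Name any further covariates before unblinding, on prognostic or design grounds, and say whether they enter the primary or a sensitivity model. The stratification factors (gender, baseline anxiety, physical activity level) are natural candidates.

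The cost is one or two sentences in the protocol or analysis plan. T0 BDI-II and the stratification factors are already collected, and the sample size need not change. Dropping p-values from the baseline table is a reporting preference and not part of the required change.

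### Cohen's d for BDI-II is defined from unadjusted change scores rather than the baseline-adjusted ANCOVA difference, so it is less precise and moves with chance baseline imbalance

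*Protocol article*

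**What the plan says.** All the relevant text is in the protocol article.

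- **Primary analysis (Statistical analysis).** "Analysis of covariance (ANCOVA) for the BDI-II score at T1 will be conducted as the primary analysis". The covariates follow in the same sentence: "with the BDI-II score at T0 and other characteristics with significant between-group difference at T0 as covariates in the model for sensitivity analyses". As worded, it is not fully clear whether the T0 score is in the primary model or only in the sensitivity models.
- **Effect size (Statistical analysis).** "Effect size estimates will be obtained for the primary outcome", with the between-group Cohen's d "calculated using the mean differences from baseline and the SDs of the two groups at each time point". The section does not say whether these are SDs of raw scores or of changes.
- **Planning values (Sample size).** In the cited previous trial, "mean (standard deviation) of BDI-II score at baseline for intervention and usual group were 19.18 (8.35) and 17.68 (9.52) respectively". The pooled SD of 8.95 is then used "to detect the difference of 3.5 points in BDI-II with a common standard deviation of 8.95", which gives the planned standardised effect of 0.39.
- **Stratification (Randomization, concealment and blindness).** The factors are gender, anxiety symptoms and physical activity level. Baseline BDI-II is not among them.

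**The concern.** The estimate behind the primary p-value and the estimate behind the published d come from two different calculations on the same data. ANCOVA subtracts from the T1 difference only the part of the baseline difference that carries forward to T1. A change score subtracts all of it. If one arm starts higher by chance, the change-score contrast over-corrects and favours that arm.

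Baseline BDI-II is not a stratification factor, so chance imbalance on it is not directly controlled. The published d could then sit visibly above or below what the ANCOVA supports, and readers and meta-analysts often carry forward the d. A more precise estimate is already available from the planned models. The divisor adds a smaller difficulty: because it is taken visit by visit, d at T1, T2 and T3 can differ through spread alone.

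**Working it through.** **1. The plan's own figures reproduce.**
- Pooled SD = √((8.35² + 9.52²)/2) = 8.95.
- Planned d = 3.5/8.95 = 0.391, stated as 0.39.
- Sample size: the stated test is "at a significance level of 0.05 using two-sided t-test". With 80% power the noncentral t gives 103.6, so 104 per group (power 0.801).
- With 20% dropout, 104/0.80 = 130 per group, 260 in total.

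**2. Gap between the two numerators.** Let ΔX be the baseline difference between arms, ΔY the T1 difference, and b the within-group slope of T1 on T0.
- Change-score difference = ΔY − ΔX.
- ANCOVA difference = ΔY − bΔX.
- Change-score minus ANCOVA = −(1 − b)ΔX.

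With equal SDs at both visits, b equals the T0-T1 correlation ρ. The article gives no value for ρ, so 0.4 to 0.7 is assumed.

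**3. Relative precision.** With common SD σ, the numerator variances are proportional to 2σ²(1 − ρ) for change scores and σ²(1 − ρ²) for ANCOVA. Their ratio is 2(1 − ρ)/(1 − ρ²) = 2/(1 + ρ).

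**4. Numbers.** For illustration, ΔX = 19.18 − 17.68 = 1.50 points, the gap in the cited trial.

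| ρ (assumed) | Shift in points, 1.5(1 − ρ) | Shift in d (÷ 8.95) | Share of 3.5 points | Variance ratio |
|---|---|---|---|---|
| 0.4 | 0.90 | 0.10 | 26% | 1.43 |
| 0.5 | 0.75 | 0.08 | 21% | 1.33 |
| 0.6 | 0.60 | 0.07 | 17% | 1.25 |
| 0.7 | 0.45 | 0.05 | 13% | 1.18 |

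At ρ = 0.5, a true adjusted d of 0.391 would be reported as 0.475 or 0.307, depending on which arm started higher.

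**5. How large a chance gap is likely here.** The SE of the baseline difference is 8.95√(2/n): 1.11 points at 130 per group and 1.24 at 104. The 95% ranges are ±2.18 and ±2.43 points. A gap of 1.5 points or more in either direction has probability of about 18% at 130 per group and 23% at 104. The mean absolute gap at 130 per group is about 0.9 points, which at ρ = 0.5 shifts d by about 0.05. A gap of 2.43 points at ρ = 0.5 shifts it by 0.136. These figures ignore any indirect balancing of BDI-II through stratification on anxiety.

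**6. Simulation.** There were 4,000 trials for each ρ, with 104 per group, SD 8.95 and a true difference of 3.5 points. Both versions of d were divided by the T1 SD.

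| ρ | Mean change-score d | Mean ANCOVA d | 95th percentile of absolute gap | Correlation with baseline gap: change-score, ANCOVA |
|---|---|---|---|---|
| 0.3 | −0.396 | −0.394 | 0.197 | −0.61, −0.01 |
| 0.5 | −0.394 | −0.394 | 0.142 | −0.50, 0.00 |
| 0.7 | −0.393 | −0.393 | 0.087 | −0.39, −0.01 |

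The averages agree, so there is no systematic bias. The single-trial values differ, and only the change-score d follows the baseline gap.

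**7. Divisor.** A fixed 3.5 points gives 3.5/7 = 0.50 or 3.5/10 = 0.35 for assumed visit SDs of 7 and 10. If change SDs are meant, the divisor is 8.95√(2(1 − ρ)), and the same 3.5 points gives 0.357 at ρ = 0.4 and 0.505 at ρ = 0.7.

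**The case against.** The strongest reply is that this is a matter of reporting convention. Both contrasts estimate the same treatment effect under randomisation. The size is also modest: a shift of 0.05 to 0.10 lies well inside d's own sampling error, with a 95% half-width of about 1.96√(2/104) = 0.27 at 104 per group. The 1.5-point gap belongs to another trial and would be exceeded here in only about one trial in five. All of this stands, and it sets the grade. It does not defend the formula, because a better numerator comes at no cost from models already planned.

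Four stronger readings are tempting, and the article does not support them.

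- **The p-value and d answer different questions, or d is biased.** They share an estimand under randomisation, and the simulated averages coincide.
- **d is the trial's headline result.** The article names BDI-II at T1 as the primary outcome and ANCOVA as the primary analysis. No test, decision or sample size rests on d.
- **The reported d cannot be compared with the planned 0.39.** The 8.95 comes from baseline data, but Sample size uses it as the common SD for a difference at 4 months after randomisation. A d over the T1 raw-score SD is a fair counterpart. The baseline SD as divisor is a convention that the plan does not require.
- **The visit-specific SD undermines the T1 result.** One visit has one pooled SD. The issue arises only when d is compared across visits, and the models also give differences in points.

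The choice between raw-score and change SDs may be settled in an analysis plan that is not shown, so it is not a fault in itself. The numerator is stated in the article and can be judged as written.

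**Conclusion.** The point holds as a minor matter of consistency and precision. As written, d for BDI-II uses an unadjusted change-score contrast, which in the realised trial departs from the baseline-adjusted difference by (1 − b) times the chance baseline gap. For an assumed correlation of 0.7 to 0.4, the numerator variance is about 18% to 43% higher than under ANCOVA, and a 1.5-point gap shifts d by about 0.05 to 0.10.

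The conclusion rests on three assumptions: the correlation range, equal SDs at T0 and T1, and a primary ANCOVA that includes T0 BDI-II. The last is the natural reading but is not cleanly stated. If the primary model left T0 out, the change-score contrast would differ from it by the whole baseline gap (1.5/8.95 = 0.17 SD in the example). The primary test, 104 per group and 260 in total are untouched.

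**What to change.** Replace the definition of d in Statistical analysis with one that states:

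- **Numerator:** the baseline-adjusted between-group difference, from the ANCOVA with T0 BDI-II as covariate at T1 and from a baseline-adjusted mixed model at T2 and T3.
- **Divisor:** one named raw-score SD, the same at all visits. The pooled baseline SD is one reasonable choice. What matters is that it is named in advance.
- **Reporting:** d with a confidence interval, beside the adjusted difference in BDI-II points and its interval.

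The same edit should say plainly that T0 BDI-II is a covariate in the primary ANCOVA. The cost is a sentence or two, settled before any analysis by arm. No new data, model or participants are needed. At the planning values, d stays at 3.5/8.95 = 0.39.
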